### Data analysis

2.10

#### Analysis populations

2.10.1

In the ENERGYCO project, per-protocol and intention-to-treat (ITT) approaches, as well as sensitivity analyses, will be conducted. On one hand, the per-protocol approach will be used to present the main and secondary analysis. Participants from the intervention group who have cycled to and/or from school at least 3 days/week over 8 weeks will be included. Additionally, participants from both the intervention and control groups must have valid data at baseline and follow-up for the outcomes of interest (e.g., RMR and PAEE). On the other hand, the ITT approach will be used to present main and secondary analysis, but in the Supplementary material. This approach will include all participants in both the intervention and control groups who have valid data at baseline and follow-up or who have missing data at either baseline or follow-up. Finally, the potential impact of missing data will be assessed using various imputation models and sensitivity analyses. Specifically, we will conduct sensitivity analyses to determine whether the choice of imputation method affects the results. Additionally, no interim analyses will be performed.

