
**Table 1 tab1:** Schools’ inclusion and exclusion criteria.

Inclusion criteria	Exclusion criteria
The school has a specific space for parking bicycles and allows their parking	The school does not have specific infrastructure to park or store bicycles
The school has at least two classes per grade	The school offers bus transportation to the adolescents
At least eight students from the school will agree to participate in the study	The school is already participating in other interventions focused on promoting healthy behaviors
Schools from urban areas	The school has implemented an intervention to encourage commuting to school within the last year
	Schools from rural areas

**Table 2 tab2:** Participants’ inclusion and exclusion criteria.

Inclusion criteria	Exclusion criteria
Adolescents’ females and males aged from 12 to 17 years old (both ages included)	Adolescents younger than 12 years or older than 17 years
Healthy participants who can ride a bicycle safely and without difficulty.	Participants with any injury or medical condition that prevents safe participation in cycling to and from school
Be able to cycle to and from school at least 3 days per week during eight consecutive weeks (Intervention group)	Insufficient ability to ride a bicycle or inability to cycle to and from school at least 3 days a week (Intervention group)
Not to cycle to and from school more than 3 days a week during the last year	Participants who have cycled to and from school more than 3 days a week during the past year
To present a valid signed consent from their parents or legal guardians	Participants without a valid, signed parental or guardian consent form
To present valid data at baseline and follow-up from all the outcomes assessed	Participants who do not provide valid data for all assessed outcomes at baseline and follow-up

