#### Statistical analysis

2.10.2

Descriptive analyses of all study variables presented with the mean (standard deviation) and frequencies (percentage) will be performed. Subsequently, the normality of the variables will be analyzed using histograms and normality tests. In Phase I, for the comparison of PAEE between the different modes of commuting (i.e., walking, cycling, and motorized-vehicle), a repeated measures ANOVA will be performed using the per-protocol approach. In addition, Student t-test or Mann–Whitney tests will be performed to compare the fluctuation of PAEE according to speed or distance commuted between active modes of commuting (i.e., walking vs. cycling).Within Phase II, the effects of the school-based cycling intervention on RMR and other health-related outcomes will be studied using an analysis of covariance (ANCOVA). Post-intervention RMR and other-health related values will be included as dependent variables, group (i.e., experimental group vs. control group) as fixed factor, and baseline outcome data as covariates. To evaluate the effect of the intervention on the secondary outcomes (i.e., physiological, physical, and psychosocial outcomes), we will conduct the same analysis used for the main outcomes (i.e., ANCOVA analysis using the intention-to-treat approach). Moreover, to control the variability between schools, the analyses will include adjustments for contextual and organizational variables, such as the SES of the school area, the length of cycling lanes, the availability of bicycle parking, and the level of engagement of teachers and students in the intervention. The estimates will be present as raw and standardized (z-scores; i.e., mean differences between follow-up and baseline data divided by the standard deviation), as an indication of the change the post-intervention z-scores will be calculated relative to the baseline mean and standard deviation. Effect sizes will be categorized as small (0.2 SDs), medium (0.5 SDs), and large (0.8 SDs), based on Cohen (93). Finally, to analyze the influence of covariates on the association between the intervention and the main outcomes (i.e., RMR and PAEE), mediation analyses will be performed. The intervention will be included as the independent variable, and the main outcomes as the dependent variables. Covariates included in the mediation analysis will encompass body composition, physical function, cognitive determinants, perceived barriers or autonomy, built-environment characteristics, weather, among others. In the statistical analysis, a value of *p* < 0.05 will be considered statistically significant.

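### The main analysis is per-protocol, with an adherence filter in the intervention arm only, so the headline effect does not compare the groups as randomised; a second section labels that analysis intention-to-treat

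*Protocol article*

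**What the plan says.** Section 2.10.1 (Analysis populations) ranks the analyses: "the per-protocol approach will be used to present the main and secondary analysis". It defines that set by two filters.

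- Adherence, intervention arm only: "Participants from the intervention group who have cycled to and/or from school at least 3 days/week over 8 weeks will be included".
- Data completeness, both arms: "participants from both the intervention and control groups must have valid data at baseline and follow-up for the outcomes of interest".

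ITT is also planned, in second place: "the ITT approach will be used to present main and secondary analysis, but in the Supplementary material". That set keeps participants with data missing at baseline or follow-up, and sensitivity analyses of the imputation method are foreseen.

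Section 2.10.2 (Statistical analysis) says of the secondary outcomes that they will receive "the same analysis used for the main outcomes (i.e., ANCOVA analysis using the intention-to-treat approach".

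Table 2 lists among the participant inclusion criteria: "To present valid data at baseline and follow-up from all the outcomes assessed". Section 2.4.1 places randomisation of schools after the baseline assessment.

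**The concern.** The trial asks whether the intervention raises resting metabolic rate and physical activity energy expenditure relative to control, which is a superiority question. Randomising schools is meant to make the arms comparable. An adherence filter observed after randomisation, and applied in one arm, gives that up: selected intervention adolescents are compared with every control who has data.

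Those who pass are plausibly more motivated, fitter or closer to school. The article itself names family reasons, distance and predisposition as limits on who can take part (section 2.4.1) and expects variable adherence (Discussion). ANCOVA on the baseline outcome removes only the part of this selection that the baseline value carries. It does not remove selection on motivation or on change over time.

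Since section 2.10.2 can be read as naming ITT for the same outcomes, either population could be presented as the main one after the results are known.

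**Working it through.** **The sections side by side.** No figure in the plan decides this point; it turns on the text.

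| Place | Population for the main outcomes |
|---|---|
| 2.10.1 | Per-protocol is the main presentation; ITT is in the supplement |
| 2.10.2 | ANCOVA, described as ITT |
| Table 2 | Valid follow-up data on all outcomes needed for inclusion |

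The Table 2 row can be checked only after follow-up. Applied literally, it removes the participants with missing follow-up whom the ITT definition in 2.10.1 keeps, and ITT becomes a completer set.

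**Size of the bias under a true null (illustration).** From the plan: 300 adolescents allocated 1:1, so 150 per arm, and a 5% two-sided test (section 2.4.2). Assumed, and not in the documents: the share p of the intervention arm that passes the filter, and the correlation r between the tendency to adhere and the baseline-adjusted outcome. Clustering is ignored.

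Shift in SD units = r × φ(z)/p, with z = Φ⁻¹(1 − p). Standard error = √(1/n₁ + 1/n₂), with n₁ = 150p and n₂ = 150. The rejection rate is the two-sided normal probability beyond 1.96 given shift/SE.

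- p = 0.85: φ(z)/p = 0.2332/0.85 = 0.274; n₁ = 128; SE = 0.120.
- p = 0.60: φ(z)/p = 0.3863/0.60 = 0.644; n₁ = 90; SE = 0.133.

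| p | r | Shift (SD) | False-positive rate |
|---|---|---|---|
| 0.85 | 0.1 | 0.027 | 5.6% |
| 0.85 | 0.3 | 0.082 | 10.5% |
| 0.60 | 0.1 | 0.064 | 7.7% |
| 0.60 | 0.2 | 0.129 | 16% |
| 0.60 | 0.3 | 0.193 | 30.5% |

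If controls also lost 15% (n₂ = 128), the last row would be 29%. Section 2.4.2 places the 15% dropout in the experimental group, so 150 controls is closer to the plan. The 85% row borrows that dropout figure as a lower anchor for exclusion; dropout is not the same as non-adherence.

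**What ITT costs in power.** Read the plan's effect size of 0.25 as Cohen's f, which is d = 0.5 for two equal groups. Suppose d = 0.5 holds in adherers only and non-adherers gain nothing. With 60% adherence the ITT effect is 0.60 × 0.5 = 0.30. At 150 per arm SE = √(2/150) = 0.1155, 0.30/0.1155 = 2.60, and power is about 74% before clustering. With 85% adherence the effect is 0.425 and power about 96%. The plan's stated power is 95%.

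**Adherence wording.** Section 2.10.1 counts a day with a trip in either direction; the target in section 2.8 is both directions. The minimum is 3 × 8 = 24 trips under one wording and 6 × 8 = 48 under the other. These are minimum counts, not expected exposure.

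**The case against.** Four points can be made for the plan.

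1. **A randomised analysis exists.** A reader might infer that ITT is missing or will be suppressed. The documents do not support that: ITT is prespecified for main and secondary outcomes, with imputation sensitivity analyses, and section 2.11 commits to publishing whatever the findings show. This stands. The fault is ITT's rank, not its absence.

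2. **The two sections may be compatible.** Because 2.10.1 runs the main and secondary analyses under both approaches, the parenthesis in 2.10.2 could describe the supplementary version. That is possible, so an outright contradiction would be too strong a reading. But the sentence does not say so, and the same section expressly assigns per-protocol to Phase I. The two sections need reconciling.

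3. **The bias may be small.** A reader might infer a false-positive rate of 16% or more. That rests on 60% passing and correlations of at least 0.2, neither of which is documented. At 85% passing the rate is about 6 to 11%. This stands as a limit on the size. It does not restore the randomised comparison.

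4. **The adherence wording is secondary.** The Table 2 row ("Be able to cycle to and from school at least 3 days per week during eight consecutive weeks (Intervention group") is an entry criterion on ability, not a definition of adherence, so the relevant comparison is with the target in section 2.8. The 8-week condition could also be read as an average over the period rather than a requirement in every week. Both points stand; the wording still decides who enters the set now called main.

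**Conclusion.** The point holds. As written, the headline effect compares adherent intervention adolescents with all controls who have data, not the groups formed by randomising schools, and the article supports two different headline populations.

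The selection plausibly favours the intervention. Its size cannot be known from the documents: about 0.03 SD and 6% false positives at 85% passing and correlation 0.1, up to about 0.19 SD and 29 to 31% at 60% passing and correlation 0.3. This assumes no true effect, a normal tendency to adhere and no clustering. The argument about ranking depends on none of these numbers. It should be settled before analysis because it determines the main estimate of the trial.

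**What to change.** - In 2.10.1, make ITT the main analysis of primary and secondary outcomes: every adolescent enrolled in a randomised school, analysed as allocated, with the planned missing-data handling. Report per-protocol as supplementary and label it non-randomised.
- Make 2.10.2 name the same population as 2.10.1.
- Remove valid follow-up data from the inclusion and exclusion criteria in Table 2, so that ITT does not shrink to completers.
- Reconcile the one-direction-or-both wording in 2.10.1 with the both-directions target in 2.8, and say whether the 8-week condition applies to each week or on average.

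An instrumental-variable estimate of the effect in adherers is not a ready substitute. Non-adherers in intervention schools still receive the Bikeability sessions and the weekly challenges, so the assumption that allocation acts only through cycling is doubtful. If such an estimate is reported, it should carry that caveat.

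**Cost.** No new outcome measures are needed, since both analyses are already planned, but this is more than an exchange of tables. Non-adherers have to be measured at follow-up, while section 2.4.1 ties the voucher to completing the 8 weeks and section 2.9 lets the principal investigator decide whether someone unable to cycle 3 days a week remains in the study; both need checking against that aim. The ITT effect will be smaller if non-adherers benefit less, with the loss of power shown above, and the sample-size section should acknowledge this.

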#### Statistical analysis

2.10.2

Descriptive analyses of all study variables presented with the mean (standard deviation) and frequencies (percentage) will be performed. Subsequently, the normality of the variables will be analyzed using histograms and normality tests. In Phase I, for the comparison of PAEE between the different modes of commuting (i.e., walking, cycling, and motorized-vehicle), a repeated measures ANOVA will be performed using the per-protocol approach. In addition, Student t-test or Mann–Whitney tests will be performed to compare the fluctuation of PAEE according to speed or distance commuted between active modes of commuting (i.e., walking vs. cycling).Within Phase II, the effects of the school-based cycling intervention on RMR and other health-related outcomes will be studied using an analysis of covariance (ANCOVA). Post-intervention RMR and other-health related values will be included as dependent variables, group (i.e., experimental group vs. control group) as fixed factor, and baseline outcome data as covariates. To evaluate the effect of the intervention on the secondary outcomes (i.e., physiological, physical, and psychosocial outcomes), we will conduct the same analysis used for the main outcomes (i.e., ANCOVA analysis using the intention-to-treat approach). Moreover, to control the variability between schools, the analyses will include adjustments for contextual and organizational variables, such as the SES of the school area, the length of cycling lanes, the availability of bicycle parking, and the level of engagement of teachers and students in the intervention. The estimates will be present as raw and standardized (z-scores; i.e., mean differences between follow-up and baseline data divided by the standard deviation), as an indication of the change the post-intervention z-scores will be calculated relative to the baseline mean and standard deviation. Effect sizes will be categorized as small (0.2 SDs), medium (0.5 SDs), and large (0.8 SDs), based on Cohen (93). Finally, to analyze the influence of covariates on the association between the intervention and the main outcomes (i.e., RMR and PAEE), mediation analyses will be performed. The intervention will be included as the independent variable, and the main outcomes as the dependent variables. Covariates included in the mediation analysis will encompass body composition, physical function, cognitive determinants, perceived barriers or autonomy, built-environment characteristics, weather, among others. In the statistical analysis, a value of *p* < 0.05 will be considered statistically significant.

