In this regard, given that the young population commutes to and from school at least twice on a school day, promoting active modes of commuting, mainly walking or cycling (13), has been considered as an effective strategy to improve their health (14). Indeed, scientific evidence shows that active commuting to and from school (ACS) is associated with higher levels of total PA (15), during weekdays (16), and it even appears that those adolescents who walk to school also are more active in other contexts (17, 18). In fact, such is its impact on PA levels, that in the meta-analysis conducted by Campos-Garzón et al. (19), they indicated that actively commuting to and from school may help to complete 48% of the PA recommendations in young population. Nevertheless, few studies have analyzed the PAEE related to ACS (12, 20) and to the best of our knowledge, no study has analyzed how ACS impact on RMR. Moreover, while it is well known that walking and cycling are active modes of commuting to school, they can provide different health benefits (14). Cycling to school could be more related to physical fitness and physiological improvements such as, increasing in cardiorespiratory fitness levels and overall health (14), contributing to reducing the risk of cardiovascular diseases, obesity, diabetes or depression (14, 21–24). Therefore, although ACS has several associative benefits, it is important to know the differences between walking and cycling when promoting it (25).

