Therefore, this protocol describes the rationale and methodology of the ENERGY expenditure of school Commuting study (The ENERGYCO study). ENERGYCO project will address the gaps and limitations in the existing scientific literature regarding the PAEE that occurs during cycling to school. Considering the previous literature and existing gaps, the ENERGYCO project will be divided into two phases. Phase I will focus on using a portable metabolic system to assess PAEE associated with different modes of commuting (i.e., walking, cycling, motorized vehicles) under free-living conditions in Spanish adolescents. Additionally, Phase I will serve to develop a predictive equation that will be used in Phase II to measure PAEE associated with different modes of commuting to and from school. Additionally, considering the ongoing debate regarding the health benefits of ACS and the scarcity of studies examining the effects of school-based cycling interventions on RMR and PAEE, the Phase II will aim to assess the effects of a school-based cycling intervention on RMR and PAEE, as well as on other physiological (i.e., basal heart rate, blood pressure, and body temperature), physical (i.e., PA levels, anthropometric measures, body composition, physical fitness, and motor competence), and psychosocial outcomes (e.g., perceived barriers to active commute to school, self-esteem, and mental health) on Spanish adolescents. It is hypothesized that, in Phase I, using a portable metabolic system under free-living conditions will provide accurate and distinct measurements of PAEE associated with different commuting modes in Spanish adolescents. Specifically, we hypothesize that these measurements will highlight significant differences in PAEE across commuting modes, offering a more precise understanding of how commuting impacts adolescents’ physical activity levels. Additionally, we expect the data collected in Phase I to contribute to the development of a valid and reliable predictive equation for estimating PAEE during commuting to and from school. we hypothesize that a school-based cycling intervention will lead to a significant increase in both RMR and PAEE compared to a control group. We further hypothesize that the intervention will improve physiological outcomes (e.g., reductions in basal heart rate), physical outcomes (e.g., enhanced physical fitness and motor competence), and psychosocial outcomes (e.g., increased self-esteem) among Spanish adolescents.

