#### Study assessment protocol

2.6.1

In Phase I, participants will perform three different simulations (i.e., commute by motorized-vehicle, walking, and cycling [see Figure 2]): (1) a simulation of driving to school will be performed by motorized-vehicle. After all the calibration process of the Cosmed K5 (both, flow and gas analyzers will be calibrated before every gas exchange measurement), a face-mask attached to the K5 will be place and gas exchange will be check during a two-minute period before the measurement start. After the check phase, gas exchange recording start during a five-minute period, while participants remain seated. Then, the participants will simulate commute in a motorized-vehicle by remaining seated in a chair for another 15-minute period, having previously walked for 2 mins simulating that participants are moving toward the motorized-vehicle from home. After this first simulation, there will be a five-minute period of cooling down. The total time of this first test will be 27 min. (2) A simulation walking to school will be conducted in a closed circuit defined by the research staff. The same procedures mentioned before will be followed. Then, the participant will walk for 15 min (the participant will determine the speed and intensity of walking) and finish with a five-minute cool down; (3) Participants will simulate a cycling route. They will wait for five-minute after walking and they will start cycling during 15-minute period along the designated route. The simulation will finish with a five-minute cool down period. The total time used in the walking and cycling simulations will be 45 min. These times were chosen because an average walking speed of 4.4–4.6 km/h would not exceed the distance Spanish adolescents are willing to walk to their educational center (1,350 m) (52). While no study in Spanish adolescents indicates the distance, they are willing to cycle to school, we estimated a distance of 4,200 m, the threshold distance used for Australian adolescents (53), with which a speed of approximately 15 km/h would not exceed 15 min. Detailed visual information on the evaluation and calibration process of the Cosmed K5 (Cosmed, Rome, Italy) can be found at the following link.^1^ In order that one active mode of commuting (e.g., walking) does not affect the post exercise oxygen consumption, thus PAEE, of the subsequent active mode of commuting (e.g., cycling), participants will alternate randomly by first performing the simulation of walking or cycling. In addition, the alternation of starting on the bike and walking will be counterbalanced by having the same number of participants starting on the bike or walking. Finally, all data will be downloaded using PC OMNIA.9 software v3.30.79 (Cosmed, Rome, Italy).

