It is important to mention that the ENERGYCO protocol presents some limitations and risks that may arise in the future. These limitations will be: (i) some participants may not attend the assessments, which could lead to a small sample size; (ii) the relatively small sample size in Phase I, which could potentially limit statistical power and generalizability. The sample size was determined based on previous studies using indirect calorimetry in similar research contexts. However, the complexity of the data collection process posed significant challenges for recruitment; (iii) important outcomes such as distance or barriers to cycling to school may also influence the recruitment process, resulting in a low-rate recruitment; (iv) there may be problems with the selection of schools. In Phase II, after the selection of schools, it is possible that there may not be enough students to form each of the groups to low prevalence of cycling to and from school in Spain (46); (v) the family is not involved in the intervention, uncertainties surrounding the help that the school can give to the research group for the success of the intervention (e.g., contact with adolescents). On the other hand, the ENERGYCO protocol presents several strengths. The study design is a cluster randomized controlled trial, as well as the duration of 8 weeks of the school-based cycling intervention, including strategies for maintaining adherence and motivation, and an incentive system. The use of instruments gold standard, such as the Omnical for assessing the RER, or the use of indirect calorimetry for measuring the PAEE related to different modes of commuting will provide accurate data for these variables.

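### The Phase I mode comparison rests on a per-protocol set defined only for Phase II, and its three-mode test cannot inform on cycling versus walking

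*Protocol article*

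**What the plan says.** Phase I recruits a convenience sample of 50 adolescents (Section 2.2) and is cross-sectional (Section 2.1). Section 2.6.1 has a within-person design: "participants will perform three different simulations". In the vehicle condition, after a 2-minute walk, "the participants will simulate commute in a motorized-vehicle by remaining seated in a chair for another 15-minute period".

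For the comparison of PAEE between the three modes, Section 2.10.2 says that "a repeated measures ANOVA will be performed using the per-protocol approach". It then adds that "Student t-test or Mann–Whitney tests will be performed to compare the fluctuation of PAEE according to speed or distance commuted between active modes", walking versus cycling. It does not say that this second test is paired.

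Section 2.10.1 defines the per-protocol set. Intervention participants must have cycled on at least 3 days a week for 8 weeks, and participants in both arms must have valid data at baseline and follow-up. The same section promises, for the project as a whole, imputation models and sensitivity analyses for missing data.

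On purpose, the Introduction says "we hypothesize that these measurements will highlight significant differences in PAEE across commuting modes", and earlier that "it is important to know the differences between walking and cycling when promoting it". Table 3 lists energy expenditure as a primary outcome and marks it for Phase I as well as Phase II. The Discussion concedes "the relatively small sample size in Phase I, which could potentially limit statistical power and generalizability".

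**The concern.** Two parts of the stated Phase I analysis do not fit the Phase I design.

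First, the analysis set. Phase I has no arms, no 8-week programme and no follow-up, so no Phase I participant can be classified by the per-protocol definition given. An analyst would have to invent a rule for who enters the test, possibly after seeing the traces.

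Second, the test. The omnibus null says that all three modes have equal mean PAEE. One mode is mostly sitting, so that null is false whether or not cycling and walking differ. A significant result would support the hypothesis as worded and leave open the comparison that bears on promoting one active mode over the other. The remaining walking-cycling test does not close this gap: it concerns how PAEE fluctuates with speed or distance, and one of its two options treats the two modes as separate groups of people.

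A further cost is precision. The classical method uses only participants with a usable trace in every mode, in a sample that the protocol already calls small.

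**Working it through.** The documents give no Phase I effect size, SD, correlation or missing rate, so there is no planned figure to reproduce. The inputs from the protocol are n = 50, three modes per participant and alpha = 0.05. Everything else below is assumed and shown over a range.

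**1. Analysis set.**

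| Per-protocol element (2.10.1) | Counterpart in Phase I |
|---|---|
| Intervention and control groups | None; everyone does all three modes |
| Cycling 3 days a week over 8 weeks | None; a 15-minute bout per mode |
| Valid baseline and follow-up data | None; cross-sectional |

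The intention-to-treat set in the same section is also worded by arm, baseline and follow-up, so it offers no substitute.

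**2. Omnibus test when walking equals cycling.** Take means (0, d, d) in SD units, with SD 1 and common correlation rho. The grand mean is 2d/3, so the sum of squared deviations is (4/9 + 1/9 + 1/9)d² = 2d²/3. The noncentrality is lambda = n × (2d²/3)/(1 − rho), with 2 and 2(n − 1) = 98 degrees of freedom.

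- d = 0.25: lambda = 2.08 (rho 0) to 6.94 (rho 0.7); rejection 23% to 64%.
- d = 0.5: lambda = 8.33 to 27.8; rejection 72% to 99.8%.
- d = 0.75: lambda = 18.75 to 62.5; rejection 97.6% to about 100%.
- d = 1: lambda = 33.3 to 111; rejection about 100%.

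In 20,000 simulated trials per setting with d = 1 and rho 0.3, 0.5 or 0.7, the omnibus test rejected in about 100% and a paired walking-cycling t-test in 4.9% to 5.2%, its nominal level. In natural units, assumed means of 300/900/900 ml/min with a CV of 15-20% also gave 100% omnibus rejection. At a CV of 20% the gap there is 600/180 = 3.3 SDs of the active modes.

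**3. Unpaired test on paired data.** An unpaired test uses variance 2σ²/n where the true variance of the mean difference is 2σ²(1 − rho)/n. Simulated on walking and cycling means, a nominal 5% unpaired t-test had a true size of 2.1%, 0.6% and 0.05% at rho 0.3, 0.5 and 0.7. It is conservative, so it loses power. The Mann-Whitney test ignores the pairing in the same way; it was not simulated.

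**4. Participants with all three modes.** If a share m of traces per mode is unusable, independently across modes, completers number 50(1 − m)³. The all-bouts variance comes from summing the generalized least squares information over all missing-data patterns, with equal SDs, known covariance and data missing completely at random.

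| m | Completers of 50 | Variance of cycling − walking, completers relative to all bouts (rho 0.3 to 0.7) |
|---|---|---|
| 5% | 42.9 | 1.08 to 1.10 (1.09 at rho 0.5) |
| 10% | 36.5 | 1.18 to 1.21 (1.19 at rho 0.5) |
| 15% | 30.7 | 1.29 to 1.33 (1.31 at rho 0.5) |

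Interval width grows by the square root: at rho 0.5 about 4%, 9% and 14%. If nothing is lost, the ratio is 1.

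**The case against.** Repeated measures ANOVA is a standard method for three conditions on the same people. The stated hypothesis is about differences across modes, and the omnibus test addresses exactly that; if seated and active PAEE differ, rejection is correct. Post hoc pairwise tests and sphericity corrections are details that an article may leave to an analysis plan. The Introduction's remark on walking versus cycling closes a paragraph on health benefits and does not itself name a Phase I contrast. Phase II takes the predictive equation from Phase I, not this test. All of this stands, so unnamed post hoc tests are not the point here.

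Three stronger readings are tempting and not supported.

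- A reader might infer that the omnibus test must reject. It need not: at a gap of 0.25 SD it rejects in only 23% to 64% of trials, and the documents do not give the gap.
- A reader might infer that the plan prescribes a completers-only analysis. It does not say so. That restriction follows from the classical method, and the promised imputation-based sensitivity analyses might soften it. Trace failures may also cluster within participants: if a participant's three traces always failed together, 10% loss would leave 45 completers, no partial data and nothing to recover.
- A reader might infer that walking and cycling are not compared at all. Means and SDs are promised for all variables, and a t-test or Mann-Whitney test is named. What is not fixed is a paired estimate of the PAEE difference with its interval.

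What survives is in the text itself: an analysis set that cannot be applied, and a named walking-cycling test with an option that contradicts the within-person design.

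**Conclusion.** The point holds in limited form. That the per-protocol definition cannot be applied to Phase I follows from Sections 2.1, 2.10.1 and 2.10.2 alone and needs no assumption. That the omnibus test does not inform on cycling versus walking also follows from its null hypothesis; that it will almost surely be significant holds for a seated-active gap of about 0.75 to 1 SD or more at n = 50, which is realistic for sitting against walking or cycling but is not documented. The mismatch between Mann-Whitney and paired data is plain from the design.

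The loss of precision is conditional. It is roughly 9%, 19% or 31% in variance if 5%, 10% or 15% of traces per mode are lost independently and completely at random, less if losses cluster, and nil if there are none. The consequence is confined to what Phase I can claim about particular modes; the Phase II comparison of arms does not depend on this test. The change is worth making because a better method costs almost nothing.

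**What to change.** In Section 2.10.2, or in the analysis plan if one exists:

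- Replace the Phase I repeated measures ANOVA with a linear mixed model on all available bouts, with mode as fixed effect and an unstructured within-participant covariance.
- Report cycling minus walking PAEE with its 95% CI, and the two contrasts with the vehicle mode with Holm adjustment.
- Base Phase I conclusions about particular modes on these contrasts. An overall test can stay as support for the across-modes hypothesis.
- For Phase I, replace the per-protocol approach with all participants who have at least one valid bout.
- Make any walking-cycling test paired, including the one on speed or distance.

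The cost is wording and standard software, with the same data and no added burden on participants. The gain in precision arises only if some traces are lost; the gain in clarity does not depend on that.
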